#### Collection of saliva

2.13.6

Samples of unstimulated saliva (2 mL) will be collected in 50 mL tubes (Falcon tube). In the laboratory 500 μL of pure saliva will be added to 500 μL Tris/EDTA, and stored at −80° C (freezer from the UNINOVE Biophotonics Laboratory).

#### Extraction of DNA

2.13.7

The DNA extraction will be performed with Meta-G-Nome DNA Isolation - MGN0910 (Epicenter Technologies Corp, Chicago, IL) according to the manufacturer's instructions. For saliva samples and HSV secretion, 100 μL of sample, previously mixed in a Vortex at 12,857*g* (10,000 RPM), 4° C, shall be transferred for 10 minutes to new centrifuge microtubes. The supernatant will be discarded, leaving 25 μL, next to the precipitate. Samples will be mixed in a Vortex for resuspension of the pellet. For each sample a mixture of 2 μL of proteinase K and 300 μL of TCL (tissue and cell lysis), placed in a water bath for 15 minutes and every 5 minutes will be vortexed. After the water bath, the samples will be placed on ice for 5 minutes. About 150 μL of protein precipitation solution reagent and mixed in a Vortex for 5 seconds. It will be centrifuged for 10 minutes, 4°C at 12,857*g* (10,000 RPM). The supernatant will be discarded, leaving only the pellet. About 500 μL of isopropanol will be added and the samples will be poured 40 times. The samples will then be centrifuged again for 10 minutes, at 4°C at 2057*g* (4000 RPM), the samples being poured, removing the isopropanol, leaving only the pellet. About 200 μL of 70% ethanol will be added and centrifuged for 2 minutes, 4°C and 2057*g* (4000 RPM). The ethanol will be withdrawn and the last step will be repeated. The tubes will be opened, inverted to dry, for about 30 minutes. After drying, the resulting pellet will be eluted in Tris/EDTA. After DNA extraction the samples will be stored in a freezer at −20°C and quantified through the spectrophotometer (Nanodrop ND1000; Thermo Fisher Scientific Inc). Prior to polymerase chain reaction (PCR) amplification, a set of primers for HSVP1/P2 corresponding to a DNA sequencing the eight human herpes virus described by Johnson et al (Table 2) will be used. The first HSVP1/P2 amplifies the subtypes HSV-1, HSV-2, Epstein-Barr virus, and cytomegalovirus.^[33,34]^

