### Study variables and time

2.12

The primary study variable will be evaluation of the resolution time of the lesions in days (primary objective of the study). For this, a 15-day follow-up will be performed for this variable.

The secondary variables of the study will be

Follow-up of the recurrences of herpes simplex labialis (HSL) lesion at baseline (T0), 1 (T3), 6 months (T4), and 1 year (T5) follow-up periods.Presence of ballooning cells by exfoliative cytology at baseline (T0) and 3 (T1) days after injury.Evaluate if the amount of HSV-1 decreases after treatment with aPDT by Quantitative polymerase chain reaction q at the baseline (T0), 3 (T1), and 7 (T2).Evaluation of cytokines interleukin (IL)-6, IL-1β, IL-8, tumor necrosis factor alpha (TNF-α), and IL-10 by enzyme-linked immunosorbent assay method in nonstimulated saliva and HSL lesions in the baseline (T0), 3 (T1), 7 (T2), and 30 days after treatment (T3).To verify the presence of pain in HSL patients by HSL VAS at baseline (T0), 3 (T1), 7 (T2), and 30 days after treatment (T3).Check the temperature at the site of HSL lesion at baseline (T0), 3 (T1), 7 (T2), and 30 days after treatment (T3).Quality of life perception of HSL patients related to oral health will be assessed using the OHIP-14 questionnaire at baseline (T0) and 30 (T3) days after treatment.

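### The DNA extraction steps in section 2.13.7 keep the protein pellet and discard the liquid that should hold the DNA for the HSV-1 qPCR

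*Protocol article*

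**What the plan says.** Section 2.13.7 (Extraction of DNA) names a commercial kit, says its maker's directions are followed, and then gives the bench steps for saliva and lesion secretion alike:

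- A 100 μL sample is spun, and "The supernatant will be discarded, leaving 25 μL, next to the precipitate".
- Proteinase K (2 μL) and a tissue and cell lysis reagent (300 μL) are added, with a water bath and then ice.
- Next comes "About 150 μL of protein precipitation solution reagent and mixed in a Vortex for 5 seconds", followed by a 10-minute spin at 12,857g.
- After that spin: "The supernatant will be discarded, leaving only the pellet".
- About 500 μL of isopropanol is added. The tube is spun, the isopropanol is removed, and the pellet is washed twice in 70% ethanol.
- Finally, "After drying, the resulting pellet will be eluted in Tris/EDTA". The extract is read on a spectrophotometer before PCR.

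The extract serves a secondary variable in section 2.12: "Evaluate if the amount of HSV-1 decreases after treatment with aPDT", by qPCR at T0, T1 and T2. The Discussion also lists day-30 saliva among the collections for virus quantification.

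**The concern.** Lysis puts the DNA into solution. The next reagent is named for what it brings down, which is protein. The spin after it should therefore leave protein in the pellet and DNA in the liquid, yet the text discards the liquid. The alcohol that would precipitate DNA is added only later, to what remains.

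The qPCR is the trial's direct measure of antiviral effect. If the step were carried out as printed, the amount of DNA reaching PCR would depend on how much happened to be trapped in the protein pellet. That would be low and would vary from tube to tube for reasons unrelated to viral load. The step is the same in both arms, so it favours neither, but it would blur the comparison and push it towards no difference.

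**Working it through.** The section states no summary figure to reproduce. The check is to follow which fraction is kept at each spin, and then to see whether the volumes fit.

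**Fraction kept at each spin (section 2.13.7)**

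| Spin | Where the DNA should be, by the section's own reagents | Text keeps | Coherent? |
|---|---|---|---|
| Before lysis | Unlysed material in the precipitate | Precipitate plus 25 μL | Yes |
| After protein precipitation | In solution | Pellet only | No |
| After isopropanol | Precipitated in the pellet | Pellet | Yes |
| After each ethanol wash | Pellet | Pellet | Yes |

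Only the second spin keeps the wrong fraction. No step moves its supernatant to a new tube, and no other section corrects it.

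**Volumes**

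Liquid at the disputed spin = residual + proteinase K + lysis reagent + precipitation reagent = 25 + 2 + 300 + 150 = about 477 μL.

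Isopropanol added next = about 500 μL, and 500 / 477 = 1.05 volumes.

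About one volume of isopropanol fits precipitating DNA out of that liquid. It has little purpose on a pellet whose liquid has already gone. The paragraph's own quantities therefore point to the supernatant as the fraction meant to go forward.

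**Spin figures, checked for a second error**

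12,857 / 2,057 = 6.25, and (10,000 / 4,000)² = 6.25. The g and RPM values agree, so the fault is confined to the one step.

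**Samples that pass through the step**

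- Section 2.12 schedule, two specimen types at three times: 24 × 2 × 3 = 144 for 24 completers; 30 × 2 × 3 = 180 for 30 patients.
- With the day-30 saliva in the Discussion, three lesion times and four saliva times: 24 × (3 + 4) = 168; 30 × (3 + 4) = 210.

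These counts show exposure to the step. They do not show how much DNA is lost.

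**Material left for a repeat extraction**

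- Lesion swab, stored in 500 μL (section 2.13.5): 500 − 100 = about 400 μL.
- Saliva, 500 μL mixed with 500 μL Tris/EDTA (section 2.13.6): 1,000 − 100 = about 900 μL.

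**The case against.** The strongest reply is that this paragraph does not govern the laboratory. It defers to the kit maker's instructions, which are not shown, and staff may simply follow those. The wording around the step also suggests translation trouble: the same paragraph has tubes poured 40 times, apparently meaning inverted, and elsewhere the vesicle stage becomes a gallbladder and the tube of cream a catheter. The isopropanol volume supports this reading, because it implies that the usual procedure was intended and one sentence came out wrong.

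This stands as far as intent goes: a slip is quite possible. It does not remove the point. The sentence is complete, sits in sequence, and tells the reader to do something that defeats the extraction. This is a stated step, not detail left out of a condensed article.

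A reader might go further and infer that the qPCR would find next to no viral DNA, that the secondary outcome could not be answered, and that the samples would be lost for good. The documents do not support that:

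- Some DNA may stay in the pellet, and no loss fraction can be derived.
- Only 100 μL of each stored sample is used, so extraction could be repeated without collecting again.
- The spectrophotometer reading before PCR might reveal a gross failure, although it is not specific to HSV and no acceptance limit is given.

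**Conclusion.** The point holds as an error in the written procedure. Taken literally, section 2.13.7 discards the fraction that should contain most of the DNA, and both the order of reagents and the ratio of about 1.05 volumes of isopropanol show this.

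The conclusion about DNA loss rests on two assumptions: that the named reagents do what their names say, and that the text is followed in preference to the kit instructions. If the laboratory follows the kit and the kit keeps the supernatant, only the text is wrong.

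The reach is limited to one secondary outcome, HSV-1 quantity, through 144 to 168 samples for 24 completers or 180 to 210 for 30 patients. Lesion resolution time (the primary outcome) and the sample size do not depend on it, and the cytokine assays use separately stored material. The harm is recoverable if it is noticed while residual sample remains.

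**What to change.** Before the first sample is processed, check the whole paragraph against the kit instructions it cites. Then correct the step after the protein-precipitation spin: transfer the supernatant to a clean tube, discard the protein pellet, and add the isopropanol to the supernatant. Make the same correction in the laboratory's working procedure.

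The cost is one corrected sentence in section 2.13.7 and one in the bench procedure. It needs no extra samples or reagents and no change to the design.

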### Pretreatment evaluations

2.7

Patients will sign the ICF and the TC, the anamnesis, the OHIP-14 questionnaire, and the data collection injury and questions regarding injury. Saliva and HSV secretions from all patients will also be collected for evaluation of inflammatory cytokines and saliva and HSV secretion for HSV quantification. Treatment will then be performed according to randomization.

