#### HSV-1 quantification

2.13.5

Collection of HSV lesions secretion: HSV lesion secretion samples will be collected at 1 single site in the central portion of the lesion with sterile swab after treatment of all HSV lesions. They will be stored in 500 μL of Tris-ethylenediaminetetraacetic acid in tubes of 1.5 mL for microcentrifuge (Eppendorf, Hamburg, Germany). During the collection period (in the clinic) the samples will be stored on ice inside a styrofoam. These samples will be properly identified and stored at −80°C (freezer from the UNINOVE Biophotonics Laboratory) until further analysis.

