
This study will be a double-blind clinical trial with the goal of not inducing the researcher who will treat the patient to a positive aPDT result as well as to mask the participant's type of treatment. Blocked randomization was performed so that if there is any interruption of work for any reason, we will have groups with proportional numbers of participants, allowing comparison between them. After approval by the Research Ethics Committee of the Universidade Nove de Julho, patients will be invited to participate in the study by signing the ICF. If the lesions are in the vesicle stage, they will be topically anesthetized with 2% lidocaine gel, as directed by the Research Ethics Committee. Exfoliate cytology of the lesions will be performed as it is a simple and reliable method of confirming HSV infection, according to Barret et al. Microscopically we can observe changes in cytoplasm and nuclear structures. Lange et al,^[41]^ observed that cells exhibit a space between inclusion and the extended “bull's eye” cell membrane. In addition, he observed little frequency of ballooning cells, which are pathognomonic cells in herpes lesions.

Unstimulated saliva collection will be performed before treatment, 3, 7, and 30 days after the procedure, in both groups, to quantify the virus by qPCR and to evaluate the cytokines IL-6, IL-1β, IL-8, TNF-α, and IL-10. For HSV-1 amplification by qPCR, a set of HSVP1/HSVP2 primers will be used, which corresponds to DNA sequencing the eight human herpes virus described by Johnson et al. This primer amplifies HSV-1 subtypes, HSV-2, Epstein-Barr virus, and cytomegalovirus.^[32,33,42]^

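### The only primer pair described for the secondary HSV-1 quantity endpoint is not HSV-1-specific, and the lesion swab timing in 2.13.5 conflicts with the pre-treatment baseline

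*Protocol article*

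**What the plan says.** Section 2.12 of the protocol article lists among the secondary variables: "Evaluate if the amount of HSV-1 decreases after treatment with aPDT", measured by quantitative PCR at T0, T1 (3 days) and T2 (7 days). The opening of the Methods says that virus is quantified both at the lesion and in saliva.

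On the assay, the Discussion states: "For HSV-1 amplification by qPCR, a set of HSVP1/HSVP2 primers will be used". Section 2.13.7 describes what the pair detects: "The first HSVP1/P2 amplifies the subtypes HSV-1, HSV-2, Epstein-Barr virus, and cytomegalovirus". The Discussion says the same again: "This primer amplifies HSV-1 subtypes, HSV-2, Epstein-Barr virus, and cytomegalovirus".

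On sampling, 2.7 (Pretreatment evaluations) has saliva and lesion secretion collected for HSV quantification, and then: "Treatment will then be performed according to randomization". Section 2.13.5, which gives the working instructions for the lesion swab, has it taken "in the central portion of the lesion with sterile swab after treatment of all HSV lesions". It mentions no swab before treatment. For saliva, the Discussion puts the first collection before treatment.

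**The concern.** There are two separate problems.

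**Specificity.** The endpoint names one virus. The primer pair assigned to it detects four, by the article's own account. If the quantity reported is the signal from that pair, it is a sum over whichever of the four viruses are present. A fall could not be credited to HSV-1. Conversely, a real fall in HSV-1 could be partly hidden by DNA of another herpesvirus that the local treatment leaves unchanged.

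**Timing.** A baseline for a treatment effect has to precede treatment. Two sections say so for the lesion sample, and the section that staff would follow at the chairside says otherwise. If 2.13.5 is followed at T0, the lesion baseline already contains whatever the procedure did to the virus at the site, and the procedure differs between the arms. A sample taken at the wrong moment cannot be repaired later.

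**Working it through.** **1. Endpoint against assay.**

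| Item | Where | Content |
|---|---|---|
| Target | 2.12 | HSV-1 |
| Primer pair assigned to the HSV-1 qPCR | Discussion | HSVP1/HSVP2 |
| What the pair detects | 2.13.7 and Discussion | HSV-1, HSV-2, Epstein-Barr virus, cytomegalovirus |
| Other quantification step named | 2.13.7 | Spectrophotometry of the DNA extract, which measures DNA and is not virus-specific |

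The visible text names no HSV-1-specific primer, probe or typing step. The mismatch is stated by the document itself, so it needs no outside source.

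**2. Size of the attenuation (illustration only).** Assume that a share *f* of the baseline signal comes from the other viruses, that treatment leaves this part unchanged, and that all targets amplify equally. For a true HSV-1 fall of *k* log10,

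apparent fall = −log10( *f* + (1 − *f*) × 10^−*k* ).

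With *k* = 2:

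| *f* | *f* + (1 − *f*) × 0.01 | Apparent fall (log10) |
|---|---|---|
| 0.1% | 0.01099 | 1.96 |
| 1% | 0.0199 | 1.70 |
| 10% | 0.109 | 0.96 |
| 30% | 0.307 | 0.51 |
| 50% | 0.505 | 0.30 |

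Neither *f*, nor *k* = 2, nor equal amplification comes from the documents. The table shows how the loss depends on *f*. It does not estimate the loss in this trial.

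**3. Timing of the lesion swab.**

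| Section | Lesion sample for HSV quantification |
|---|---|
| 2.7 | Before treatment |
| 2.12 | A T0 (baseline) value is required |
| 2.13.5 | After all lesions have been treated |

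Let *D* be the log10 fall from the true pre-treatment level to day 3 in an arm, and *I* the part already present just after the procedure. A pre-treatment T0 swab gives a change of *D*. A post-procedure T0 swab gives *D* − *I*. The between-arm contrast then becomes (*D*₂ − *D*₁) − (*I*₂ − *I*₁), so it is biased whenever the immediate effect differs by arm. Section 2.10 makes a difference plausible. Before that swab, G2 would have received methylene blue, active irradiation and a saline wash. G1 would have received the vehicle, a switched-off laser and a wash. The documents give no value for *I*, so the bias cannot be sized.

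**4. Saliva.** Section 2.7 and the Discussion both place the first saliva sample before treatment, and no section contradicts them. The timing conflict therefore concerns the lesion swab only.

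**The case against.** **The assay may be more specific than the text shows.** The primer table (Table 2) is not visible. Section 2.13.7 calls HSVP1/P2 the first set, which may imply a second, and introduces it as a step before PCR amplification. An article may also leave a probe, typing or melt-curve step to the full protocol. This stands as a limit on the claim: one cannot say that the trial is unable to measure HSV-1. It does not remove the point, because the Discussion names this pair, and no other, for HSV-1 amplification by qPCR, and the article twice describes the pair as detecting four viruses.

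**The baseline is in fact specified.** Sections 2.7 and 2.12 provide for it. Section 2.13.5 deals mainly with site, buffer and storage, does not mention T0, and could be describing the day-3 and day-7 swabs. The parallel lesion-swab text for cytokines in 2.13.8 has no such phrase. This also stands. A reader might infer from 2.13.5 that change from baseline cannot be measured at all, but the documents do not support that. They contain a contradiction about one sample type, not an absent baseline.

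**The attenuation figures have no anchor in the documents.** Agreed. Nothing shows that the share of other viral DNA in a swab from the centre of a herpes lesion is large, and at 0.1% the loss is negligible. The failure of attribution does not depend on the size of *f*, because an assay limited to this pair does not reveal *f*.

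**Conclusion.** The point holds in a limited form. As described, the assay for the secondary HSV-1 endpoint does not allow its signal to be attributed to HSV-1. An unaffected non-target share would pull an apparent fall towards zero, by an amount that the documents do not let anyone fix. This conclusion assumes that no specific primer, probe or typing step sits in Table 2 or the full protocol.

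The instruction in 2.13.5 contradicts 2.7 and 2.12 for the lesion swab and has to be reconciled with them. The bias by arm arises only if 2.13.5 is followed at T0.

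The stronger reading, that the endpoint can measure neither HSV-1 nor its change, goes too far on both counts. The matter is worth correcting before sampling starts, but it is confined to one secondary variable.

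**What to change.** 1. Quantify the endpoint with an HSV-1-specific primer or probe, and keep HSVP1/HSVP2 at most as a screen. If Table 2 or the full protocol already contains a specific set, name that set as the one used for the endpoint in 2.12 and 2.13.7.
2. Reword 2.13.5 so that the T0 lesion swab is taken before treatment in both arms, as in 2.7, with the later swabs at T1 and T2.

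The first change costs a small assay set-up effort within a qPCR that is already planned. The second costs one sentence. Neither adds visits or samples.

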**Table 2 T2:**
[figure not shown]
Sequence and reference of primer.

#### Salivary cytokine profile and HSV lesion secretion

2.13.8

The HSV lesion secretion samples will be collected with sterile swab at 1 site (central lesion site) and stored in 1.5 mL tubes for microcentrifuge (Eppendorf). The collected samples will be stored on ice. These samples will be properly identified and stored at −80°C (UNINOVE Biophotonics Laboratory) until further analysis.

#### Saliva collect

2.13.9

Samples of unstimulated saliva (2 mL) will be collected in 50 mL tubes (Falcon tube) requesting that the patient spit in a 50-mL centrifuge tube without touching the lips at the edges of the tube on the 1st care. In the laboratory, 1 mL of pure saliva will be stored in 1.5 mL centrifuge tubes at −80°C (freezer from the Biophotonic Laboratory of UNINOVE).^[35]^ Analysis of salivary cytokine profile and HSV lesions: Determination of salivary levels and HSV secretions of the inflammatory markers TNF-α, IL-1β, IL-6, IL-8, and IL-10 will be performed. Cytokine levels will be determined using high sensitivity 8-plex human cytokine by Millipore (Millipore Corporation, Billerica, MA). The miliplex kits will be developed with microspheres and based on immunoassays.

#### Pain

2.13.10

Pain will be assessed by applying the VAS with a line of 100 mm, with both ends closed. One end has the indication “0” and the other “10” which means respectively no pain and unbearable pain. Instructions for marking will always be given to the patient by the same operator. Each patient will be instructed to mark with a vertical trace the point that best corresponds to the intensity of pain at the time of evaluation.^[36]^

#### Temperature

2.13.11

The temperature will be measured at the site of the lesion (at its central point) and at its side (healthy skin 2 cm from the edge of the lesion). The local measurement will be measured using the Safety 1st digital thermometer (Safety 1st Montreal Quebec Canada) (Safety 1st, “No Touch Forehead: Xi’an, China,” Columbus, OH).^[36]^

#### Oral health impact profile (OHIP-14)

2.13.12

This questionnaire is a simplified form of the original OHIP-49 questionnaire,^[37]^ the OHIP-14, and will be used to assess the impact of oral health on the quality of life of the research participants. The OHIP-14 is used to measure perceived needs. It measures the impact of oral changes on oral health related quality of life. The patient responds to 14 questions by assigning to his answers the values 0 (never), 1 (almost never), 2 (sometimes), 3 (most of the time), and 4 (always) (Table 3).

**Table 3 T3:**
[figure not shown]
Questions of OHIP-14.

It can be analyzed under 2 optics:

1.Additive method: The points are summed (0–56), with 56 being the greatest impact on quality of life.2.Domain evaluation: OHIP-14 has a total of 7 domains, which can also be scored from 0 to 4, with 4 being the highest impact. To get the result, add the 2 questions of each domain and divide by 2. Domain 1 refers to functional limitation, domain 2 refers to physical pain, domain 3 refers to physical limitation, domain 4 refers to psychological discomfort, domain 5 refers to psychological inability, social discomfort, and domain 7 refers to general disability (Table 4).

**Table 4 T4:**
[figure not shown]
Domains of the OHIP-14 questionnaire.

It will be evaluated at the 1st attendance, after 7 days, if there is any recurrence, and after 1 year the OHIP-14. In the additive method, when the value is >1, the presence of a negative impact on the individual's life may be considered.

The justification for this work is the viral resistance that the continuous use of aciclovir can promote^[7,10]^ and that PDT has shown good results but to date there are no clinical trials, only case reports^[15,20,29]^ and, in addition, PDT can prevent HSL recurrence.^[7,38–40]^

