## Introduction

1

The prevalence of herpes labialis increases gradually in childhood, reaching 70% to 80% of adults worldwide.^[1–3]^ Recurrence of herpes occurs in 20% to 40% of the world's population.^[4]^ Herpes labialis are an infectious disease caused by the herpes simplex virus (HSV). HSV type 1 (HSV-1) and HSV-2 subtypes affect the skin and mucous membranes, but the HSV-1 subtype affects the orofacial region more. Recurrent herpes labialis can also be known as “fever blisters” or “cold sores.”^[5]^ Initial primary infections are usually more severe than recurrent ones, since the patient does not have acquired immunity.^[6]^ Herpetic gingivostomatitis usually occurs in young children characterized by painful oro-labial vesicles that coalesce and rupture forming ulcers, lasting between 10 and 14 days, accompanied by fever, malaise, fatigue, pain muscle, and dehydration.^[6–9]^

Clinically, the recurrence of the lesions goes through stages: prodromal, redness, papule, gallbladder, ulcer, crust, dry scaling, and remission of the lesion. Many of these stages may be short or imperceptible.^[6,10,11]^ It is a self-limiting, painful disease that generates discomfort, social restraint, and aesthetic compromise. In immunocompromised patients, recurrent lesions are more aggressive and take longer to heal.^[12,13]^ Because of these factors, associated with several recurrences, studies are important for other alternatives to treat herpes labialis, aiming to a fast resolution of the lesions, with less time of recurrence, without undesirable side effects.

Aciclovir is the most widely used medication to prevent or suppress HSV-1.^[10,14]^ Continuous use of these drugs may develop a high viral resistance.^[7,10]^ Antiviral medications are most effective when the patient is still in the prodromal phase. Aciclovir is effective in reducing the duration and symptoms of infection, but the optimal dose is still unknown.^[9]^ Although acyclovir decreases the duration of symptoms, it does not prevent recurrence.^[15–17]^ In view of the resistance that antiviral treatment can cause and the recurrence of the lesion, some alternative treatments have been studied, such as antimicrobial photodynamic therapy (PDT), which is a good option.^[18]^

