The PDT is a therapeutic option in many fields of medicine.^[19]^ It is selective and noninvasive, also indicated for transplant and oncology patients.^[15]^ It consists of the combination of a chromophore agent, such as methylene blue, at a certain concentration, associated with monochromatic laser light at a given wavelength.^[20]^ The photosensitizer (methylene blue) absorbs visible laser light at a suitable wavelength (660 nm) from the ground state to the singlet state, which has a short shelf life. From there, the photosensitizer can lose energy through nonradioactive, radioactive (phosphorescence) processes, or generate reactive oxygen species (ROS) through 2 mechanisms: either by electron transfer, forming free radicals (type I reactions), or through the transfer of energy to molecular oxygen forming singlet oxygen (type II reactions).^[21]^ The lesions of herpes labialis are recurrent in some patients, causing pain, aesthetic commitment, and absenteeism in the work. Your complete remission lasts until 15 days. Treatment with acyclovir decreases painful symptoms; however, it causes viral resistance and does not prevent recurrence of the lesions. It is known that antimicrobial PDT (aPDT) has numerous advantages among them the reduction of the time of remission and, moreover, does not cause resistance; although there are still no well-designed clinical studies that prove its effectiveness, there are only case reports. Therefore, the objective of this study will be to evaluate whether PDT is able to reduce the healing time of these lesions and decrease their recurrence.

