### Statistical analysis

2.14

Statistical analysis will be performed using only the data obtained from the patients who complete the study. The Kolmogorov–Smirnov test will be applied before the analysis of the normality of each parameter. The *t* test will be used to compare all means. All tests will be performed using Graphpad Prism 5 (Graphpad Software, San Diego, CA). Data will be presented on average and ±standard deviation. The level of significance will be set at *P* < .05.

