In addition, the inflammatory markers TNF-α, IL-1β, IL-6, and IL-8 and IL-10 will be determined by 8-plex high sensitivity human cytokine per Millipore (Millipore Corporation, Billerica, MA), where Marques Filho et al^[43]^ found high levels of these cytokines in the crevicular fluid of patients with peri-implantitis. In the experimental group, methylene blue will be delicately placed and with a 1-minute wait for the photosensitizer to interact with the tissue according to Alvarenga et al.^[43]^ The parameters used for laser application will be performed according to Ramalho et al^[29]^ in case studies reported using 0.005% methylene blue photosensitizer, with the laser head in contact with the lesion, perpendicularly, 3 J energy for 30 seconds, with diode laser at 660 nm wavelength in a single session. Marotti^[20]^ used the laser at the same wavelength, with an energy density of 120 J/cm^2^, with a power of 40 mW, with 2 minutes per point and 4.8 J energy at each point and with 4 points around the lesion in herpes lesions in the vesicle phase, breaking them prior to the application of methylene blue, in which it was used at a concentration of 0.01% (the use of 0.005% is explained based on the large quantity of works with good results). The total energy delivered was 19.1 J. Twenty-four hours after the 1st application, the procedure was repeated, but with energy density of 3.8 J/cm^2^, 15 mW of power, with 0.6 J of energy at the same previously irradiated points, and these parameters were repeated after 72 hours and after a week. There was a decrease in the frequency of vesicle recurrence. De Paula Eduardo et al,^[13]^ found in a literature review that in cases where aPDT was indicated in the vesicle phase, there was a reduction in vesicle title as well as lesion duration. Decreased signs of infection and symptoms are reported within hours of aPDT application, provided they are used at a wavelength around 660 nm and with the appropriate photosensitizer. Based on these studies, we expect a reduction in the time of resolution of lesions, as well as the recurrence of lesions, providing a low cost alternative indicated for patients with viral resistance to the gold standard drug, acyclovir, and, offering an alternative in immunocompromised patients who have a high recurrence of herpetic lesions and in patients who should avoid drug administration by organ impairment where acyclovir is metabolized, as well as in healthy patients who have a high recurrence of lesions, decreasing discomfort.

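### OHIP-14 scores triggered by a recurrence fall under the blanket t test, so that one comparison covers only patients who recur and is not protected by randomisation

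*Protocol article*

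**What the plan says.** Three parts of the protocol article bear on this point.

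- **When OHIP-14 is given.** Section 2.13.12 (text after Table 4): "It will be evaluated at the 1st attendance, after 7 days, if there is any recurrence, and after 1 year the OHIP-14". Section 2.12, which lists the secondary variables, gives a different schedule: quality of life "will be assessed using the OHIP-14 questionnaire at baseline (T0) and 30 (T3) days after treatment". It mentions no score at recurrence.
- **How it is analysed.** Section 2.14 has one method for continuous outcomes: the t "test will be used to compare all means". It sets no event-triggered measurement apart. The analysis set is also given there: "Statistical analysis will be performed using only the data obtained from the patients who complete the study".
- **What PDT is expected to do to recurrence.** The objective in the Introduction is to "evaluate whether PDT is able to reduce the healing time of these lesions and decrease their recurrence". Section 2.13.12 adds that "PDT can prevent HSL recurrence", and the Discussion says "we expect a reduction in the time of resolution of lesions, as well as the recurrence of lesions". Of the control treatment the Introduction says: "Although acyclovir decreases the duration of symptoms, it does not prevent recurrence".

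Recurrence is also a secondary variable in its own right (sections 2.12 and 2.13.2), followed for one year.

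**The concern.** A mean score at recurrence can be formed only from patients who had a recurrence. Recurrence happens after randomisation, and on the trial's own hypothesis its frequency differs between the arms. The two groups being compared are then selected by an outcome of treatment. They need not be alike in severity or anything else, even though the randomised arms were.

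If PDT prevents episodes, patients who escape them leave this comparison altogether. It can then show nothing although PDT has lowered the burden of disease. It can also point against PDT if the patients who still recur on PDT are the more severe ones. A P value from it, reported next to the fixed-visit results, would invite a conclusion about quality of life that it cannot carry.

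**Working it through.** The article gives no figure for OHIP-14 or for recurrence by arm, so there is no stated result to reproduce. The argument rests on the text; the numbers below only illustrate it.

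**Step 1: which patients supply a score**

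| OHIP-14 time | Source | Who contributes |
|---|---|---|
| First attendance / baseline | 2.12, 2.13.12 | everyone |
| 7 days | 2.13.12 | everyone attending |
| 30 days | 2.12 | everyone attending |
| Any recurrence | 2.13.12 | only patients who recur |
| 1 year | 2.13.12 | everyone attending |

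Only the fourth row is defined by an event that treatment may change.

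**Step 2: expected contrast.** From the article: 12 per group (section 2.1). Assumed: PDT halves the proportion with a recurrence; OHIP-14 during an episode averages 14 (SD 5) across patients and is 2 without one; PDT does not alter the score within an episode.

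If recurrence is unrelated to severity, the difference among recurrers is 14 - 14 = 0. Over all patients, each arm's mean is p × 14 + (1 - p) × 2:

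- 40% v 20%: PDT 2.8 + 1.6 = 4.4; control 5.6 + 1.2 = 6.8; difference -2.4
- 60% v 30%: PDT 4.2 + 1.4 = 5.6; control 8.4 + 0.8 = 9.2; difference -3.6
- 80% v 40%: PDT 5.6 + 1.2 = 6.8; control 11.2 + 0.4 = 11.6; difference -4.8

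If more severe patients recur more often (log-odds slope of 1 or 2 per SD of severity), a large simulation gives these PDT minus control differences:

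| Recurrence, control v PDT | Recurrers only | All patients |
|---|---|---|
| 40% v 20% | +0.97 to +1.57 | -2.69 to -2.82 |
| 60% v 30% | +1.29 to +1.93 | -3.71 to -3.76 |
| 80% v 40% | +1.62 to +2.36 | -4.49 to -4.38 |
| 40% v 40%, or 60% v 60% | 0 | 0 |

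The last row matters: with no effect on recurrence there is no selection bias.

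**Step 3: precision.** With 12 per group, 60% v 30% means 12 × 0.6 = 7.2 against 12 × 0.3 = 3.6 recurrers. The difference detectable with 80% power at two-sided 5% is (1.960 + 0.842) × √(1/n₁ + 1/n₂) in SD units, by normal approximation:

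- 12 v 12: 1.14 SD
- 10 v 5: 1.53 SD
- 7 v 4: 1.76 SD
- 5 v 2: 2.34 SD

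At 30% recurrence, the chance that the PDT arm has fewer than two recurrers is 0.7¹² + 12 × 0.3 × 0.7¹¹ = 0.014 + 0.071 = 0.085. In about 8.5% of trials the usual two-sample t test could not be run.

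**Step 4: behaviour of the test.** This is a second simulation with other assumptions: 12 per arm, SD 6, recurrence 60% v 30%. With a mean of 14 at recurrence in both arms, the recurrers-only test rejects in about 5% of trials, its nominal level. If the mean at recurrence is 17 on PDT and 14 on control, PDT has the higher mean in about 77% of evaluable trials. About 50% would be expected by chance under equal severity, and the result is significant against PDT in only about 10%.

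**The case against.** The strongest reply is that nowhere does the article name a between-arm test of recurrence-visit scores. Section 2.13.12 says when the questionnaire is given. The comparison follows only from a general sentence in a short statistics section, and the handling of unscheduled visits is often left to a fuller plan. The formal list in section 2.12 has OHIP-14 at baseline and 30 days only. This stands as a limit on how firmly the point can be put. It does not remove the point, because the article states both the trigger and a single test for every mean, with no exception. Section 2.12 conflicts with section 2.13.12; it does not override it.

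A reader might also infer that the trial gives no credit for prevented episodes, or that its quality-of-life assessment as a whole is compromised. The documents do not support that. Patients without a recurrence still have OHIP-14 scores at the fixed visits, and prevented episodes count in the separate recurrence outcome.

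Nor do the documents support a prediction that PDT will look harmful. Nothing in them says that PDT would remove the milder episodes. With equal severity the recurrers-only test keeps its 5% level.

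**Conclusion.** The point holds in a narrow form. As written, sections 2.13.12 and 2.14 together take in one comparison that is conditioned on a post-randomisation event the trial expects PDT to reduce. That comparison cannot support a between-arm conclusion on quality of life. This follows from the design and does not depend on the illustrative figures.

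The size depends entirely on assumed recurrence rates and scores. Across the halving scenarios in step 2 the recurrers-only difference is 0 to +2.4 points, against -2.4 to -4.8 over all patients. Both are zero if PDT leaves recurrence unchanged.

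It concerns one extra time point of one secondary outcome. Selection by recurrence does not touch the fixed-visit scores, the recurrence outcome or the primary outcome (time to lesion resolution). It is a minor correction.

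**What to change.** - In sections 2.13.12 and 2.14, state that OHIP-14 scores taken at a recurrence are reported descriptively by arm, with the number of patients contributing, and are not tested between arms.
- State that OHIP-14 is tested between arms only at fixed visits, in all randomised patients. For this outcome that replaces the completers-only set in section 2.14.
- Reconcile the two schedules: section 2.12 has baseline and 30 days; section 2.13.12 has first attendance, 7 days and 1 year, plus recurrences.

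A sum of recurrence scores with 0 for patients who do not recur is not needed. It would assign a value that was never measured, on a questionnaire covering oral-health impact in general, and it would largely repeat the recurrence outcome.

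The cost is a few sentences and one between-arm P value given up. The event-triggered part needs no new data. Testing in all randomised patients means seeking fixed-visit scores from those who stop early and saying how missing ones are handled.
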